## Randomization

Using a centralized computer randomization service (ROME, Population Health Research Institute, Hamilton, Ontario, Canada), we randomized patients 1:1, stratified by planned closure-device use, to femoral arterial access either with US vs with no US. All patients were to have fluoroscopy of the femoral head prior to puncture, in both groups. We considered patients randomized as soon as the treatment allocation was provided to the operator. Allocation was blinded with a variable block size.

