### Other outcomes

The key secondary outcomes include the individual components of the primary outcome. Other outcomes include the number of attempts to achieve arterial puncture, successful CFA cannulation, venipunctures, closure device failure, and the total time to obtain femoral access.

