### Angiographic core laboratory evaluation

Blinded research personnel will analyze peripheral angiograms in an angiographic core laboratory located at the Hamilton General Hospital, Hamilton, Ontario, Canada. We will tabulate the location of the femoral bifurcation, the presence of femoral artery calcification, the site of femoral artery cannulation, active bleeding, and femoral artery dissection.

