## Statistical Considerations

The initial sample size was based on the definition used in the **R**ad**i**al **v**s Femor**al** Access for Coronary Angiography or Intervention (RIVAL) trial in patients with acute coronary syndromes of major vascular complications, and the study used a 3% expected event rate in the control arm and a 1% expected event rate in the experimental arm. These assumptions led to a sample size of 1538 patients, in order to have 80% power with a 2-sided 5% type 1 error level.^12^

A limitation of our initial sample size calculation is that BARC 2 bleeding information was not collected in the RIVAL trial, and therefore it did not have an accurate assessment of event rates. As a result, we re-estimated our sample size based on blinded event rates after enrolling 450 patients. Our revised control event rate was estimated to be 14%. Subsequently, 600 patients were needed to have 80% power, a 2-sided 5% type 1 error level, and a 50% relative risk reduction for the primary outcome. We amended the protocol on April 12, 2021. Power calculations were performed using PASS (version 13, NCSS Statistical Software, Kaysville, UT). Recruitment took longer than expected due to the COVID-19 pandemic halting all non-COVID-19-related research during periods of 2020.

For the primary analysis, an intention-to-treat analysis will include all randomized patients.^13^ In this way, patients will be kept in the treatment group to which they were originally randomized. A secondary as-treated analysis will also be performed. A χ^2^ test or Fisher’s exact test will be performed on a per-patient basis, and statistical significance will be claimed if the *P* value is less than 0.05. Of note, core-lab analyses will be performed on a per-access basis. Odds ratios and 95% confidence intervals will also be reported to quantify treatment effects.

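### Core-lab comparisons are per access although patients were randomized, with no stated allowance for clustering; inference on CFA cannulation is somewhat too optimistic if some patients have two accesses (minor)

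*Protocol article*

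**What the plan says.** The unit of randomization is the patient. Under Randomization the protocol article states: "we randomized patients 1:1, stratified by planned closure-device use". A patient counts as randomized once the operator receives the allocation: "We considered patients randomized as soon as the treatment allocation was provided to the operator".

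Under Statistical Considerations, the named tests are tied to the patient (a χ² "test or Fisher’s exact test will be performed on a per-patient basis"), with the rule that "statistical significance will be claimed if the *P* value is less than 0.05". The next sentence makes an exception: "Of note, core-lab analyses will be performed on a per-access basis". The paragraph then closes with the effect measure: "Odds ratios and 95% confidence intervals will also be reported to quantify treatment effects". It names no other test, no method for correlated observations and no rule limiting a patient to one access.

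The angiographic core laboratory records the location of the bifurcation, the presence of calcification, and "the site of femoral artery cannulation, active bleeding, and femoral artery dissection". Of these, the site of cannulation feeds a listed trial outcome: "successful CFA cannulation" appears in the section Other outcomes, separately from the primary outcome and the key secondary outcomes.

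**The concern.** A per-access rule differs from a per-patient rule only when some patients contribute more than one access, so the exception itself allows for such patients. Two accesses in one patient share the patient and the assigned arm, and probably the operator. Their results are therefore likely to be positively correlated. A χ² or Fisher test on accesses, or an ordinary odds ratio with its usual interval, counts them as two independent pieces of information. The standard error is then too small, the interval too narrow and the P value too low.

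What is at stake is the inference on CFA cannulation. That outcome matters for the mechanism: the Hypothesis section rests on avoiding punctures above the inguinal ligament and below the bifurcation, and the Discussion presents the blinded core laboratory as a strength over the earlier trial that had CFA cannulation as its primary outcome.

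**Working it through.** **The plan's own figure.** The article gives no calculation for the core-lab analysis; its sample size is for the primary outcome, per patient. With 14% versus 7%, two-sided 5% and 80% power, the pooled-variance formula gives, per arm,

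n = [1.960·√(2·0.105·0.895) + 0.8416·√(0.14·0.86 + 0.07·0.93)]² / 0.07² = (0.8497 + 0.3625)² / 0.0049 ≈ 299.9, so 300 per arm and 600 in total.

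This matches the stated 600. The initial 1538 (3% versus 1%) reproduces in the same way. Both count patients, so the choice of unit for core-lab analyses does not touch them.

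**Inputs for the per-access analysis.**
- 621 patients randomized (Study status).
- f, the share of patients with two accesses: not given. Assumed 5% to 30%. The middle value, 14.2%, is numerically the share with chronic total occlusion PCI as indication in Table 3. It serves only as a convenient scale, because nothing in the article says that those patients had two accesses.
- ρ, the correlation between two accesses in one patient: not given. Assumed 0.3 to 0.8.

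**Formulae.** With a share f contributing two accesses and the rest one:
- Design effect: DE = [(1 − f) + 2f(1 + ρ)] / (1 + f) = 1 + 2ρf / (1 + f).
- Naive standard error divided by true standard error: 1/√DE.
- Actual two-sided error of a nominal 5% test: 2·[1 − Φ(1.96/√DE)].

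Example, f = 0.142 and ρ = 0.5: DE = 1 + 0.142/1.142 = 1.124; 1/√1.124 = 0.943; actual error 6.5%.

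| f | accesses from 621 patients | ρ | DE | naive SE / true SE | actual error |
|---|---|---|---|---|---|
| 0 | 621 | any | 1.00 | 1.00 | 5.0% |
| 5% | 652 | 0.3 | 1.03 | 0.986 | 5.3% |
| 5% | 652 | 0.8 | 1.08 | 0.964 | 5.9% |
| 14.2% | 709 | 0.3 | 1.07 | 0.965 | 5.9% |
| 14.2% | 709 | 0.5 | 1.12 | 0.943 | 6.5% |
| 14.2% | 709 | 0.8 | 1.20 | 0.913 | 7.4% |
| 30% | 807 | 0.3 | 1.14 | 0.937 | 6.6% |
| 30% | 807 | 0.5 | 1.23 | 0.901 | 7.7% |
| 30% | 807 | 0.8 | 1.37 | 0.855 | 9.4% |

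**Check by simulation.** A pooled two-proportion z test (equivalent to the uncorrected χ²) with 310 patients per arm, an assumed success rate of 85% and 20,000 replicates gave error rates from 5.0% (f = 5%, ρ = 0.3) to 9.7% (f = 30%, ρ = 0.8), and 7.3% at f = 14.2%, ρ = 0.8. These agree with the formula within simulation noise.

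**The case against.** The strongest objection is that this is a detail for the statistical analysis plan. The article ties the χ² and Fisher tests to the patient and names no test for the per-access analyses. It never says outright that an independence-based test will be run on accesses, and a plan that is not shown may specify a clustered method. A per-access unit is also not wrong in itself, since the site of cannulation is a property of an access. This stands in part, and it lowers the severity. It does not remove the point: the article itself chooses a unit other than the one randomized, and pairs that choice only with methods that assume independence.

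Other objections limit the scope, and they stand:
- The size rests on two undocumented quantities. With few double accesses it is negligible.
- Bifurcation location and calcification are mainly anatomical descriptors, so the concern bears chiefly on CFA cannulation.

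Two stronger readings are tempting. A reader might infer that difficult patients are over-weighted, or the arms weighted differently, because a failed first access leads to a second. The article does not support this. Under Procedures, the peripheral angiogram evaluates the position of the introducer, so a puncture that fails before sheath insertion would not ordinarily become a core-lab observation, and attempts are recorded separately. A reader might also infer that the trial's main conclusion is at risk. It is not, because the primary analysis is per patient.

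**Conclusion.** The concern holds in conditional form and is minor. Patients were randomized, the article fixes the access as the unit for core-lab analyses, and it states no allowance for clustering within patient. If some patients contribute two accesses with positively correlated results and the analysis treats them as independent, standard errors for core-lab comparisons are about 1% to 15% too small and a nominal 5% test runs at about 5.3% to 9.4%. This range rests on the assumed f of 5–30% and ρ of 0.3–0.8. With no double accesses, or no correlation, there is no effect. It would not be right to say that the intervals will be too narrow as a matter of fact, because the article does not report how many patients had more than one access.

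**What to change.** Either of two changes is enough:
- Keep the access as the unit, and estimate the odds ratios by GEE or by logistic regression with robust standard errors clustered on patient.
- Make one prespecified access per patient the main core-lab analysis, for example the first access obtained after randomization, and show all accesses as supportive. The rule must be worded in terms of the patient's randomization, because accesses themselves were not randomized.

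In both cases, report by arm the number of patients with more than one access, so that readers can judge how much the choice matters.

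The cost is a sentence of analysis wording and one model option, with no new data. Intervals become slightly wider. The one-access option also leaves the additional accesses out of the main core-lab analysis. Study status describes data collection and analyses as still under way, so the change was feasible when the article was written.

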## Subgroup Analysis

We will perform multiple a priori subgroup analyses to identify potential differing treatment effects in the following groups: age ( ≥ 75 years vs < 75 years), sex (male vs female), body mass index ( ≥ 30 kg/m^2^ vs < 30 kg/m^2^), peripheral vascular disease (presence vs absence), clinical presentation (non-ST elevation acute coronary syndrome vs elective), coronary intervention (PCI vs angiography alone), type of procedure (chronic total occlusion procedure vs nonchronic total occlusion procedure), sheath size ( ≥ 7 French vs < 7 French), planned closure device (planned vs not planned), and actual closure device use (used vs not used). The underlying hypothesis is that US-guided access will be more beneficial to higher-risk groups. No statistical adjustment will be made for multiple testing.

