## Hypothesis

Although fluoroscopy readily identifies the location of the femoral head, US allows the operator to visualize the bifurcation of the common femoral artery into superficial and profunda femoral arteries, theoretically reducing the risk of cannulating above the inguinal ligament and below the bifurcation. Furthermore, US may permit the operator to avoid puncturing areas of heavy calcium and disease, potentially reducing complications during cannulation and with closure devices. Using US may reduce the number of punctures and reduce the risk of puncture of branch vessels or venous structures, thereby potentially reducing bleeding and vascular complications.

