**Demographics and comorbidities**	
Age, y, mean (SD)	70.56 (10.24)
Female sex	158 (25.4)
BMI, kg/m^2^, mean (SD)	30.31 (23.26)
Hypertension	538 (86.6)
Dyslipidemia	555 (89.4)
Diabetes	261 (42.0)
Current smoker	92 (14.8)
Previous myocardial infarction	319 (51.4)
Previous PCI	278 (44.8)
Previous CABG	353 (56.8)
Previous stroke/TIA	58 (9.3)
Peripheral vascular disease	110 (17.7)
Atrial fibrillation	115 (18.5)
Chronic kidney disease	93 (15.0)
PCI performed during procedure	262 (42.2)

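### The prespecified subgroup by actual closure-device use is defined after randomization by something ultrasound may influence, so it can show a false interaction

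*Protocol article*

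**What the plan says.** The Subgroup Analysis section of the protocol article opens with "We will perform multiple a priori subgroup analyses to identify potential differing treatment effects in the following groups". The list has ten entries and ends with "planned closure device (planned vs not planned), and actual closure device use (used vs not used". Nothing sets the last entry apart from the other nine. The section closes with "No statistical adjustment will be made for multiple testing".

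The Randomization section says "we randomized patients 1:1, stratified by planned closure-device use", and counts a patient as randomized once the operator has been given the allocation.

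The Hypothesis section proposes that "US may permit the operator to avoid puncturing areas of heavy calcium and disease, potentially reducing complications during cannulation and with closure devices". The ultrasound steps under Treatment Groups direct the operator to look for a puncture site without anterior calcium or plaque. The Limitations section describes closure technique as a further route to preventing bleeding, and bleeding is part of the primary outcome.

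**The concern.** A subgroup analysis of a treatment effect is protected by randomization when the subgroup is fixed before allocation, or at least cannot be affected by it. Planned device use meets that condition. Actual use may not.

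If ultrasound leads to a device being used in some patients who would not have had one under palpation, device users in the two arms are different kinds of patients, and so are non-users. A difference in event rates within users then mixes any ultrasound effect with the difference in case mix.

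What is at stake is a secondary message: whether ultrasound helps more, less or not at all when a closure device is used. The Discussion expects the trial to inform guidelines, and this is a combination on which readers would look for advice.

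**Working it through.** **1. Order of events.** No single sentence says when device use is decided, so the order has to be assembled.

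- Before allocation: planned closure-device use, the stratification factor (Randomization).
- Allocation: given to the operator, who is not blinded (Design: open-label).
- After allocation: puncture and sheath insertion (Treatment Groups), then closure of that puncture.

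Actual use therefore follows randomization. Because the plan lists planned and actual use separately, it accepts that they can differ.

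**2. Can treatment affect it, and is it related to outcome?** The Hypothesis section and the ultrasound steps give a route from ultrasound to the puncture site and to complications with closure devices. That the site then affects whether a device is deployed is an inference, though a plausible one. The relation to outcome comes from the Limitations section.

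**3. Illustration with no true ultrasound effect.** The article gives no device use by arm, so all of these inputs are assumptions:

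- 25% of arteries are diseased.
- Event risk is 24% if diseased and 8% if healthy, the same in both arms. Overall risk is 0.25×24% + 0.75×8% = 12%, somewhat below the 14% control rate in Statistical Considerations.
- A device is used in 85% of healthy arteries, in both arms.
- In diseased arteries the proportion with a device is *d*, which differs by arm.

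Formulas:

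- Proportion using a device = 0.25*d* + 0.75×0.85
- Risk in users = (0.25*d*×0.24 + 0.6375×0.08) / (0.25*d* + 0.6375)
- Risk in non-users = (0.25(1−*d*)×0.24 + 0.1125×0.08) / (0.25(1−*d*) + 0.1125)

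Middle case, *d* = 0.30 in control and 0.60 with ultrasound:

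- Control: use 0.7125; users 0.069/0.7125 = 9.7%; non-users 0.051/0.2875 = 17.7%.
- Ultrasound: use 0.7875; users 0.087/0.7875 = 11.0%; non-users 0.033/0.2125 = 15.5%.
- Apparent relative risk (RR) 1.14 in users and 0.88 in non-users; ratio 1.30.

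| *d*, control vs ultrasound | RR, users | RR, non-users | Ratio of RRs | False-positive rate of interaction test, 621 patients |
|---|---|---|---|---|
| 0.30 vs 0.30 | 1.00 | 1.00 | 1.00 | 5% |
| 0.40 vs 0.50 | 1.04 | 0.96 | 1.09 | 5.4% |
| 0.30 vs 0.60 | 1.14 | 0.88 | 1.30 | about 9% |
| 0.20 vs 0.70 | 1.25 | 0.79 | 1.58 | about 16% |

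The last column is a two-sided 5% Wald test of the ratio of odds ratios (OR), with expected counts from 621 patients split 1:1. Swapping the arms inverts the ratio: 0.60 vs 0.30 gives 1/1.30 = 0.77.

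**4. A second model, to see how far the answer depends on the first.** Assume 14% risk in both arms, 50% device use in control and 60% with ultrasound, and 10% risk in patients who get a device in either arm. The risk *s* of the 10% who get one only with ultrasound is varied. The 40% who never get one carry the remaining risk: (0.14 − 0.05 − 0.10*s*)/0.40.

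- *s* = 30%: never-users 15%. Users 10% vs (0.05+0.03)/0.60 = 13.3%; non-users 18% vs 15%. ORs 1.39 and 0.80, ratio 1.72, false-positive rate about 21%.
- *s* = 5%: never-users 21.25%. Users 10% vs 9.2%; non-users 18% vs 21.25%. ORs 0.91 and 1.23, ratio 0.74, rate about 10%.
- *s* = 14%, the average risk: ratio of ORs 1.01, rate 5%.

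The direction depends on which patients are shifted, and there is almost no false interaction if they are of average risk. A real effect can be distorted as well: with a true RR of 0.50 in everyone and *s* = 30%, the apparent RR is 0.67 in users and 0.42 in non-users.

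**5. What is not affected.** The revised sample size does not involve subgroups. For 14% vs 7%, 80% power and two-sided 5%, the pooled-variance formula gives (1.96√0.18795 + 0.8416√0.1855)²/0.07² ≈ 300 per arm, which is the plan's total of 600.

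**The case against.** The strongest reply is that the key link is not in the document. The Hypothesis section says only that ultrasound may help the operator avoid diseased areas, and the benefit it names is fewer complications. It does not say that ultrasound changes whether a device is deployed. That stands: a reader might infer that the protocol itself asserts such a change, and it does not. The point rests on plausibility, which is still enough to question a subgroup presented without a caveat.

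Second, the size is assumed. In the mildest case the false-positive rate barely moves from 5%. This also stands, so the numbers show what can happen and do not predict what did.

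Third, this is one of ten secondary subgroups, and its valid counterpart is already listed, so readers could compare the two. That limits the harm, but it does not make the actual-use split interpretable.

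A reader might extend the point to other items. The documents do not support doing so:

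- **PCI and sheath size.** The split "coronary intervention (PCI vs angiography alone" and the Table 3 row "PCI performed during procedure" may reflect events after access. But being settled late is not enough; treatment must be able to affect the variable, and no route is given from puncture guidance to coronary intervention or sheath size. The Table 3 row is a description of the whole cohort.
- **Chronic total occlusion.** It appears in Table 3 as an indication for the procedure and for femoral access, so it is a reason known beforehand.
- **The outcome "closure device failure".** Its denominator is not stated, which is detail an article commonly leaves to the full plan.

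**Conclusion.** The point holds for actual closure-device use alone. The subgroup is defined after randomization by a variable that ultrasound may influence and that is related to bleeding, and the plan presents it as an ordinary a priori treatment-effect subgroup. It can produce a false interaction in either direction, or distort a true effect.

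How large this would be cannot be learned from the article. With no true effect, the first illustration gives ratios of relative risks from 1.09 to 1.58. The second gives ratios of odds ratios from 0.74 to 1.72 for a ten-point shift in use. Both need ultrasound to shift device use, and to shift it in patients whose risk differs from the rest. Without any shift, no distortion arises. The consequence is confined to a secondary analysis, so this should be corrected but does not threaten the trial's main conclusion.

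**What to change.** Remove actual closure-device use from the list in Subgroup Analysis. Keep planned closure device, which is fixed before allocation, stratifies the randomization and addresses nearly the same question.

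Alternatively, keep actual use but move it out of the treatment-effect subgroups. Report the number of patients with a device in each arm, label the table as a post-randomization description, and attach no interaction test and no claim of a differing effect.

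Either way the change is one of wording. It costs one secondary subgroup, which is lost or becomes descriptive, and leaves power and sample size as they are. The Study status section says data collection and analysis are ongoing, so it can still be made before results are reported.

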## Baseline Characteristics

The baseline characteristics of the 621 randomized patients are shown in Table 3. The patients had a mean age of 71 years; 25.4% were female; and they had a mean body mass index of 30.3 kg/m^2^. The trial population had a high rate of comorbidities: 51% had a prior myocardial infarction; 42% had diabetes; 45% had prior PCI; 57% had previous coronary artery bypass surgery; 19% had atrial fibrillation; and 18% had peripheral vascular disease. Chronic total occlusion PCI was performed in 14% of patients.

**Table 3 tbl3:** Baseline characteristics for **U**ltrasou**n**d Gu**i**dance for **V**ascular Acc**e**ss fo**r** Cardiac Procedure**s**: **A** Randomized Tria**l** (UNIVERSAL) participants

Variables	Overall
Randomized, n	621
**Demographics and comorbidities**	
Age, y, mean (SD)	70.56 (10.24)
Female sex	158 (25.4)
BMI, kg/m^2^, mean (SD)	30.31 (23.26)
Hypertension	538 (86.6)
Dyslipidemia	555 (89.4)
Diabetes	261 (42.0)
Current smoker	92 (14.8)
Previous myocardial infarction	319 (51.4)
Previous PCI	278 (44.8)
Previous CABG	353 (56.8)
Previous stroke/TIA	58 (9.3)
Peripheral vascular disease	110 (17.7)
Atrial fibrillation	115 (18.5)
Chronic kidney disease	93 (15.0)
PCI performed during procedure	262 (42.2)
**Indication for procedure**	
Atypical chest pain	83 (13.4)
Stable angina	156 (25.1)
Silent ischemia	17 (2.7)
Unstable angina	55 (8.9)
NSTEMI	123 (19.8)
Planned PCI	32 (5.2)
CTO PCI	88 (14.2)
Valvular assessment	12 (1.9)
Other	87 (14.0)
